### 2.2. Ethical Approval and Registry

This study was approved by the Ethics Committee of the University of West Attica, Greece (51758—01/06/2022) under the provision that if any important protocol modifications should occur, this will be immediately communicated to the Ethics Committee. The study will be conducted according to the stipulations of the Declaration of Helsinki “Ethical Principles of Medical Research Involving Human Subjects.” The study was also prospectively registered in the ClinicalTrials.gov database (ID: NCT05229393).

### 2.3. Setting

The co-ordination of the trial will be performed by the Physiotherapy Department of the University of West Attica in Athens. Patient recruitment will be performed from several primary care orthopedic practices from areas in the southern part of Athens. Intervention and assessment will take place in a physiotherapy practice setting, also located in the southern area of Athens, Greece. All parties involved will maintain constant contact during the patient recruitment period.

### 2.4. Recruitment Procedures

The patients will be recruited from primary care orthopedic practices located near the physiotherapy practice associated with the University of West Attica for this trial, using information leaflets and posters provided at the collaborating orthopedic practices and referrals from orthopedic or spinal surgeons.

Participants will be patients with diagnosed NSCNP of a mechanical nature, referred by orthopedic or spinal surgeons for physiotherapy, provided by their public insurance, concerning their neck pain condition. Patients will contact the physiotherapy practice to book an initial appointment, where they will be informed in detail about the objectives, methods, and details of the study via relevant written material. Clarifications will be provided by the main investigator, should any questions arise. Then, if patients agree to take part, they will be provided with a consent form to read and sign.

### 2.5. Randomization and Blinding Procedures

After the initial evaluation, random allocation of participants into the trial groups will be performed. The block randomization method will be employed, using blocks of three participants, for their distribution into the following groups: Experimental Group A: Diaphragmatic Manual Therapy (DMT) plus Cervical Manual Therapy (CMT) plus Breathing Reeducation Exercises (BREx); Experimental Group B: Cervical Manual Therapy plus sham Diaphragmatic Manual techniques; or Control Group C: Conventional Physiotherapy (CP) program. Subjects will be divided into three groups by means of balanced randomization, carried out with specialized software (http://www.randomizer.org/ (accessed on 10 May 2022)). 

Individuals will be assigned in a covert manner, using sealed, sequentially numbered opaque envelopes [21]. An impartial researcher, who is not involved in the recruitment, assessment, or intervention process, will carry out the randomization and concealed allocation. The researcher in charge of carrying out the treatment programs will only open the envelopes at the time of intervention.

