### 2.6. Participants and Eligibility

Eligible patients will be consecutively recruited. All eligible patients will be approached for recruitment into the study by the main researcher (physiotherapy practice owner), who will be responsible to book the initial appointment to inform patients about the trial’s aims, objectives, and methods and provide the consent form for them to sign, should they agree to participate. Then, another physiotherapist responsible for all data collection will perform all initial measurements on the same day. 

The principal researcher (PT) will initially assess each patient to establish their inclusion in the study. All patients will be required to provide written informed consent before being allowed to participate in the study, including consent to the publication of the results, and the patients will be informed that they are free to withdraw from the study whenever they like, without having any adverse effects on the provision of their treatment.

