### 2.7. Participants’ Characteristics

At least 90 adult volunteers of both genders, aged between 25 and 65 years, and with mechanical chronic neck pain (for more than 12 weeks), Grade I or II according to the Task Force on Neck Pain classification (Nordin 2009) [22], negative Spurling’s test, traction test, upper limb tension test, and shoulder abduction test, understanding and fluently speaking the Greek language, and the absence of another serious pathology, will be included in the present study. The diagnosis of non-specific mechanical chronic neck pain will be performed after history taking and physical examination (according to the clinical protocols of IFOMPT) [23] and medical X-rays, according to the Canadian Cervical Spine Rule (C-Spine) and the National Emergency X-Radiography Utilization Study (NEXUS) [24]. Patients will also be selected on the basis of demonstrating DB in at least one of a series of tests conducted to assess the extent of their DB (biomechanical, biochemical, psychological).

The following criteria will be used to determine who is excluded: history of cervical trauma, whiplash injury, or cervical surgery; cervical hernia; spinal degenerative disease; upper limb pain radiation; having received physiotherapeutic treatment for the cervical region within the previous three months; metabolic bone diseases and osteoporosis; cardiac or respiratory insufficiency; pregnancy; neoplasm; infectious diseases; psychological diseases; red flags (overnight pain, serious muscle spasm, weight-loss unrelated to diet, daily headache, dyspnea, confusion, and loss of consciousness); recent consumption of analgesics, anti-inflammatories, or muscle relaxants; systemic illnesses; and fibromyalgia.

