### 2.12. Interventions

Ten treatment sessions will be administered to all participants, thrice for the first two weeks and twice for the third and fourth weeks, lasting for 40 min per session. The sessions will be individually administered in a reserved room with adequate lighting, music, and air conditioning. 

The manual therapy program will be applied by a physical therapist (main researcher), a clinical instructor of manual therapy, PhD candidate, with an OMT diploma from a recognized IFOMPT program, certified as Mulligan Practitioner, with two Master of Science degrees from the Athens Medical School, Greece, and 20 years of experience in clinical practice. A physical therapist with a Master of Science degree from the Athens Medical School and 17 years of experience in clinical practice will administer the traditional physiotherapy program (Group C) and the sham diaphragmatic manual therapy component (Group B). Sham diaphragmatic manual therapy will be administered via a therapeutic ultrasound device [43]. 

The participants can only receive the assigned treatment. They will be advised against combining the treatment they were allocated to with medication or other physical therapy approaches. Any deviation from the treatment sessions administration (missing more than one appointment) or any worsening of symptoms will be reasons for exclusion. The interventions proposed for each group are described briefly below, and in detail in the Supplementary Materials. All selected interventions are widely applied in the field of physical therapy and are safe when administered by appropriately trained physical therapists. 

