### 2.14. Sample Size Calculation

The estimation of the sample size was performed with the use of the G*Power, version 3.1 program. For a three parallel groups design involving three repeated measures (pre, post-treatment, and one follow-up), in order to achieve a statistical power of 0.80 in detecting a medium effect size (Cohen’s f = 0.25) in the interaction effect, at a significance level of 5% (0.05), it was calculated that a minimum sample size of 80 individuals would be required. Taking into consideration a dropout rate of 10%, it was estimated that 30 individuals per group would need to be initially recruited [21].

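### Fixed blocks of three for three arms, with the recruiting researcher also treating two of them unblinded, can make up to a third of allocations certain and so weaken concealment

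*Protocol article*

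**What the plan says.** Section 2.5 names one block size: "The block randomization method will be employed, using blocks of three participants". It also says "Subjects will be divided into three groups by means of balanced randomization", so the ratio is 1:1:1. The target is "At least 90 adult volunteers of both genders" (Section 2.7), and in Section 2.14 "it was estimated that 30 individuals per group would need to be initially recruited".

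The roles are set out in several places:

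- **Recruitment (Section 2.6):** "All eligible patients will be approached for recruitment into the study by the main researcher (physiotherapy practice owner"). The same person books the initial appointment, explains the trial and provides the consent form.
- **Treatment (Section 2.12):** "The manual therapy program will be applied by a physical therapist (main researcher), a clinical instructor of manual therapy". Manual therapy is given in Groups A and B. A second therapist gives Group C and the sham component of Group B.
- **Envelopes (Section 2.5):** "The researcher in charge of carrying out the treatment programs will only open the envelopes at the time of intervention".
- **Site (Section 2.3):** "Intervention and assessment will take place in a physiotherapy practice setting".
- **Blinding (Section 3):** the treating physiotherapist is acknowledged to be unblinded.

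The safeguards in Section 2.5 are sealed, opaque, numbered envelopes and an independent researcher who handles randomization and concealment. Section 2.6 adds consecutive recruitment. Section 4 lists concealed allocation among the grounds for expecting high internal validity.

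**The concern.** Opaque envelopes stop a recruiter from reading the next allocation. They do not stop anyone from deducing it from earlier ones. A block of three over three arms leaves the most to deduce: after two allocations in a block, only one arm is left. The block size is published.

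The main researcher is well placed to make that deduction. The A and B patients are this person's own manual-therapy patients, and a randomized patient who goes only to the colleague must be in C. The same person approaches the next patient, books the appointment and presents the consent form.

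What is at stake is selection at entry. If the timing of bookings or the encouragement to take part shifts with the expected arm, the arms may differ in prognosis in ways that baseline adjustment may not capture. Both primary outcomes, the NDI and the pain VAS, are self-reported.

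**Working it through.** The article states no predictability figure, so there is none to reproduce.

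**Inputs.** Three arms at 1:1:1 and blocks of three (Section 2.5); 90 patients (Sections 2.7 and 2.14), hence 90/3 = 30 blocks. The guesser knows the block size and always names the most likely remaining arm.

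**Case 1: all earlier allocations in the block are known.** The chance of a correct guess is 1/3 at the first position, 1/2 at the second and 1 at the third.

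- Certain allocations: one per block, so 30 of 90 = 33.3%.
- Correct guesses: (1/3 + 1/2 + 1)/3 = 0.611, or 55 of 90. Chance alone gives 30 of 90 = 33.3%.
- Whether or not the next patient is in Group A: the six orderings of a block give 6 × 3 = 18 positions, and the answer is certain at 8 of them. That is 44.4%, or about 40 of 90. The same count holds for Group C.

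**Case 2: the latest envelope is still unopened when the next patient is approached.** The guesser knows nothing of the block at positions one and two, and one allocation at position three.

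- Certain allocations: none.
- Correct guesses: (1/3 + 1/3 + 1/2)/3 = 0.389, or 35 of 90.

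**Case 3: two envelopes pending.** Nothing in the current block is known, so guessing is at chance, 33.3%.

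**Which case applies?** The article does not give the interval from baseline to first session. Section 2.13 schedules the trial from October 2022 to June 2023, and Section 2.9 needs 16 weeks per patient. If completion means the last follow-up, about 14 to 23 weeks remain for enrolment. That is 90/23 ≈ 4 to 90/14 ≈ 6 patients per week. Some overlap is plausible at that rate, but same-day opening, or spacing of appointments by the person who books them, would restore Case 1.

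**Alternatives, with all earlier allocations known.** Fixed sizes are by exact enumeration. Mixed sizes are by simulation of lists of 90, for a guesser who knows the set of sizes but not the block boundaries.

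| Scheme | Certain | Guessed correctly |
|---|---|---|
| Fixed 3 | 33.3% | 61.1% |
| Fixed 6 | 20.0% | 56.1% |
| Fixed 9 | 14.3% | 53.2% |
| Mixed 6, 9 | about 5% | about 54% |
| Mixed 6, 9, 12 | about 2.4% | about 52% |
| Mixed 9, 12, 15 | about 2% | about 51% |

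Mixing the sizes nearly removes certainty. It leaves guessing above the 33% of chance, because an arm that lags within a block remains the better bet.

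**The case against.** The strongest case against is that 30 of 90 is a ceiling. It needs both earlier envelopes in a block to be open before the third patient is approached, and Section 2.5 has envelopes opened only when treatment starts. One pending patient takes certainty to zero. This stands, so the figures must be read as upper bounds.

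The stated limits on discretion also count. Patients are referred by surgeons and contact the practice themselves (Section 2.4), eligible patients are recruited consecutively, and all are to be approached (Section 2.6). The protocol therefore grants no freedom to choose whom to approach. That narrows the scope to act on a guess, but the person applying the rule is also the one who may know the likely arm, and booking and encouragement to consent remain in that person's hands. Section 2.6 gives the eligibility decision to a principal researcher who is not expressly identified as the main researcher.

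Opening by the treating researcher adds little, since an unblinded therapist must learn the arm. Section 2.5 speaks of one such researcher while Section 2.12 has two therapists, so who opens each envelope is unclear; the conclusion does not depend on it.

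Small blocks also have a use. They keep the arms balanced wherever recruitment stops and even out the caseload of the two therapists.

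A reader might go further and infer that every third allocation is certain whatever the timing, that concealment is defeated outright, or that the investigator would favour a particular arm. The documents support none of these. The first patient in each block stays unpredictable and the second is at best an even guess. Enrolment timing is not given, and nothing in the article bears on motive.

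**Conclusion.** The concern holds in conditional form. The block size is stated outright, so this is not a detail left to a fuller document. Combined with the overlap of recruiting and treating roles at one site, it allows up to 33% of allocations to be certain and up to 61% to be guessed. These figures assume that the recruiter knows the block size and that the earlier envelopes in the block are open. With one allocation pending they fall to 0% and 39%; with two pending, guessing is at chance.

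This is an opportunity for selection bias, not evidence that it will occur. It weakens the support that Section 4 draws from concealed allocation without contradicting it entirely. It is worth correcting before the first patient, because selection at entry cannot be repaired reliably in the analysis.

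**What to change.** 1. Replace the fixed blocks of three with randomly mixed larger blocks, for example 9, 12 and 15, generated by the independent researcher already named in Section 2.5. Withhold the sizes from recruiting and treating staff and from any public text until recruitment closes.
2. Run the list past 90, since Section 2.7 sets 90 as a minimum. A single permuted list of exactly 90 would leave no rule for the next patient.
3. Have the independent researcher release each allocation only after consent, eligibility and baseline are logged. Sections 2.5 and 2.6 already place allocation after these steps; the logged release is what is new.
4. Where existing staff allow, have someone other than the treating main researcher approach and book patients. This addresses the role overlap, which block size alone does not.

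**Cost.** A new list and a wording change; Section 2.13 says the trial had not started. Temporary imbalance between arms grows: two arms can differ by at most 1 within a block of 3, but by up to 15/3 = 5 within a block of 15. A smaller imbalance may remain if recruitment ends mid-block. Guessing falls to about 51% with certainty largely removed, but not to chance, which is why the fourth step matters.

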### 2.6. Participants and Eligibility

Eligible patients will be consecutively recruited. All eligible patients will be approached for recruitment into the study by the main researcher (physiotherapy practice owner), who will be responsible to book the initial appointment to inform patients about the trial’s aims, objectives, and methods and provide the consent form for them to sign, should they agree to participate. Then, another physiotherapist responsible for all data collection will perform all initial measurements on the same day. 

The principal researcher (PT) will initially assess each patient to establish their inclusion in the study. All patients will be required to provide written informed consent before being allowed to participate in the study, including consent to the publication of the results, and the patients will be informed that they are free to withdraw from the study whenever they like, without having any adverse effects on the provision of their treatment.

### 2.7. Participants’ Characteristics

At least 90 adult volunteers of both genders, aged between 25 and 65 years, and with mechanical chronic neck pain (for more than 12 weeks), Grade I or II according to the Task Force on Neck Pain classification (Nordin 2009) [22], negative Spurling’s test, traction test, upper limb tension test, and shoulder abduction test, understanding and fluently speaking the Greek language, and the absence of another serious pathology, will be included in the present study. The diagnosis of non-specific mechanical chronic neck pain will be performed after history taking and physical examination (according to the clinical protocols of IFOMPT) [23] and medical X-rays, according to the Canadian Cervical Spine Rule (C-Spine) and the National Emergency X-Radiography Utilization Study (NEXUS) [24]. Patients will also be selected on the basis of demonstrating DB in at least one of a series of tests conducted to assess the extent of their DB (biomechanical, biochemical, psychological).

The following criteria will be used to determine who is excluded: history of cervical trauma, whiplash injury, or cervical surgery; cervical hernia; spinal degenerative disease; upper limb pain radiation; having received physiotherapeutic treatment for the cervical region within the previous three months; metabolic bone diseases and osteoporosis; cardiac or respiratory insufficiency; pregnancy; neoplasm; infectious diseases; psychological diseases; red flags (overnight pain, serious muscle spasm, weight-loss unrelated to diet, daily headache, dyspnea, confusion, and loss of consciousness); recent consumption of analgesics, anti-inflammatories, or muscle relaxants; systemic illnesses; and fibromyalgia.

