### Objectives of the Proposed Study

Based on these findings and the hypotheses underlying the observed respiratory and psychological dysfunction in patients with NSCNP, the aims of this study will be to assess: (1) the effectiveness of manual therapy in the cervical spine (CMT) and diaphragm (DMT), in combination with breathing reeducation exercises (BREx), on musculoskeletal and respiratory outcomes in patients with NSCNP, and (2) the effectiveness of CMT alone or conventional physiotherapy (CP) on respiratory outcomes. Additionally, two additional objectives relating to the initial development of the outcome measures used in this study will be to examine: (3) the construct and concurrent validity of specific respiratory outcomes relating to DB in patients with NSCNP, and (4) the reliability of biomechanical-based assessments.

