#### 2.10.2. Concurrent Validity of Respiratory Outcomes Assessing DB

The examination of relationships between the following respiratory outcomes of DB (concurrent validity) will be performed: the NQ (psychophysiological dimension), ETCO_2_ (biochemical dimension), and RR, Hi-Lo, BHT, SBC, CVA, CWE (biomechanical dimension). Similar research has previously been conducted [41], but not in a population with NSCNP.

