#### 2.10.3. Prevalence of DB in Patients with NSCNP

As there are no established reference standards for DB [33], the diagnostic accuracy of respiratory measurements relating to DB in patients with NSCNP cannot be examined. Instead, as previously proposed [42], the prevalence of DB in patients with NSCNP can be presented, using cut-off scores established from previous studies performed in an asymptomatic population without a respiratory condition (ETCO_2_ with a cut-off score of 35 mm Hg, the NQ with a cut-off score of 19), and the Hi-Lo test, for the determination of the type of breathing, as single or combined (in pairs, or using all three) outcomes, to identify the percentage of the population with NSCNP that exhibits respiratory dysfunction. 

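### Entry requires at least one positive dysfunctional-breathing test, yet the plan describes no unselected sample for estimating how common dysfunctional breathing is in chronic neck pain or how the tests correlate

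*Protocol article*

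**What the plan says.** Section 2.7, on eligibility: "Patients will also be selected on the basis of demonstrating DB in at least one of a series of tests". The tests are those "conducted to assess the extent of their DB (biomechanical, biochemical, psychological"), so all three dimensions can qualify a patient. The individual entry tests are not listed.

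Section 2.10.3 proposes that "the prevalence of DB in patients with NSCNP can be presented". It uses end-tidal CO2 (ETCO2) "with a cut-off score of 35 mm Hg, the NQ with a cut-off score of 19", and the Hi-Lo test, "as single or combined (in pairs, or using all three) outcomes". The stated purpose is "to identify the percentage of the population with NSCNP that exhibits respiratory dysfunction".

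Section 2.10.2: "The examination of relationships between the following respiratory outcomes of DB (concurrent validity) will be performed". The measures are the Nijmegen Questionnaire (NQ), ETCO2, respiratory rate, Hi-Lo, breath holding time, single breath count, craniovertebral angle and chest wall expansion. Section 2.15 assigns Pearson correlations to this.

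On who supplies the data, section 2.10.1 ties the NQ work to a population like the one under study, and section 2.11 takes the reliability sample from the first trial participants. Sections 2.10.2 and 2.10.3 name no analysis sample. Section 2.6 has all initial measurements done on the day of consent, and section 2.5 places randomisation after the initial evaluation.

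**The concern.** The entry rule selects on the quantity that section 2.10.3 wants to estimate. The target is all patients with NSCNP, but the only sample described is NSCNP patients who have already shown DB on some test. A percentage from that sample partly reports the entry rule.

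The correlations suffer as well. Removing patients who are negative on every entry test removes the corner of the distribution where the tests agree on normality, which lowers the correlations among those that remain.

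At stake are the validity part of objective (3) and the prevalence aim. The Discussion (section 3) surmises that no single test can identify breathing dysfunction and proposes a battery. Correlations lowered by the entry rule would appear to support that premise.

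**Working it through.** The plan states no figure for prevalence, correlation or their precision, so there is nothing of its own to reproduce. The check has an exact part and an illustrative part.

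**From the documents**
- Entry condition: at least one positive DB test (2.7).
- Prevalence tests: ETCO2, NQ and Hi-Lo, singly, in pairs or all three (2.10.3). Section 2.9.2 reads the same ETCO2 and NQ cut-offs, and Hi-Lo, as indicators of DB or hyperventilation.
- Correlations: Pearson (2.15).
- Enrolled sample: at least 90 (2.7).

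**Assumed, because the documents do not give them**
- Number of entry tests: 3 (the prevalence tests only) or 6 (the measures with a DB or normal/abnormal reading in 2.9.2: NQ, Hi-Lo, breath holding time, single breath count, ETCO2, respiratory rate).
- Positivity per test in NSCNP: 30%, 50% or 70%.
- Scores: normal, all scaled so that higher is worse, with one common true correlation of 0.2 or 0.4.

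**Prevalence (exact).** For any result E that implies at least one positive entry test,

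P(E | enrolled) = P(E) / P(any entry test positive).

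This holds for single, pair and all-three prevalences built on entry tests, whatever the distribution. The share of enrolled patients with any positive entry test is 100%.

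**Correlation (simulation).** 2,000,000 draws per scenario, keeping cases with at least one positive. P(any) and prevalence are for true r = 0.2.

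| Entry tests | True positivity | P(any) | Prevalence reads | r reads (true 0.2) | r reads (true 0.4) |
|---|---|---|---|---|---|
| 3 | 30% | 0.608 | 0.30/0.608 = 49% | -0.06 | 0.07 |
| 3 | 50% | 0.827 | 0.50/0.827 = 60% | 0.03 | 0.19 |
| 3 | 70% | 0.949 | 0.70/0.949 = 74% | 0.13 | 0.29 |
| 6 | 30% | 0.797 | 0.30/0.797 = 38% | 0.10 | 0.23 |
| 6 | 50% | 0.945 | 0.50/0.945 = 53% | 0.15 | 0.30 |
| 6 | 70% | 0.991 | 0.70/0.991 = 71% | 0.19 | 0.36 |

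**Positive on any of ETCO2, NQ or Hi-Lo.** If these three are the entry tests, the enrolled figure is 100% whatever the truth. If they are three of six, at 30% positivity and r = 0.2, a true 61% reads 0.607/0.797 = 76%.

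In every scenario prevalence rises and the correlation falls. Both biases fade as P(any) approaches 1.

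**The case against.** **The denominator is not stated.** Sections 2.10.2 and 2.10.3 name no sample, whereas section 2.11 does name one for reliability. Measurements on the consent day, before randomisation, would fit a denominator taken before the DB criterion is applied. This stands as a caveat: use of the enrolled sample is an inference. But no other sample appears anywhere, and the stated target population conflicts with the stated eligibility. If a screened denominator is intended, the text has to say so, and the remedy is the same.

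**The bias may be slight.** This stands. A reader might infer that prevalence is 100% by design, or that agreeing tests will look inversely related. The first is literal only for any entry test, and section 2.10.3 does not clearly plan that estimate. The second, at r = 0.2 in the table, needs three entry tests at 30% positivity. Craniovertebral angle and chest wall expansion have no DB cut-off in section 2.9.2, and correlations with measures not used for entry shrink less.

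**Regression to the mean.** Objective (2) concerns "the effectiveness of CMT alone or conventional physiotherapy (CP) on respiratory outcomes", and a reader might infer that change from a selected baseline inflates it. The documents do not support this. The only NQ distribution they give (10 to 12 ± 7) is for healthy individuals, and entry is on any test rather than on the NQ alone. Even with mean 12, SD 7, six entry tests and an assumed retest correlation of 0.8, the enrolled-group drop is only about 0.1 to 0.7 points. Section 2.15 rests the trial on the group-by-time interaction with between-group contrasts, and the effect is shared across randomised arms.

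**Conclusion.** The point holds as a conflict between the entry criterion and the target population of the prevalence and validity work. If the enrolled sample is used as the text implies, prevalences based on entry tests are biased upward by exactly 1/P(any entry test positive), and correlations among entry tests are biased downward.

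The direction is firm, but the size is not known. It runs from a true 30% read as 49% with r = 0.2 read as -0.06, to a true 70% read as 71% with r = 0.2 read as 0.19. Where the trial lies in that range depends on which tests count for entry and how often they are positive. The common correlation and normal scores are also assumptions.

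A reader might infer that the trial itself is compromised. It is not: the criterion applies equally to all three arms, so the randomised comparison on NDI and VAS stands. The damage is confined to the prevalence aim and the validity part of objective (3).

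**What to change.** - List in section 2.7 the tests that count towards the DB entry criterion.
- Keep the DB test results of every consenting NSCNP patient who is tested, before the criterion is applied.
- State in sections 2.10.2 and 2.10.3 that this full tested cohort, including patients who then fail the criterion, is the denominator. Use it for the factor analysis in 2.10.1 too, for consistency. The working above does not quantify any harm there.
- Keep only randomised patients in the RCT analysis.
- If results from patients who fail the criterion will not be kept, drop the claim about prevalence in NSCNP and restrict the validity statements to NSCNP patients selected for DB.

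The cost is data entry and consent wording for patients who fail the criterion; their tests must be done anyway to apply it. Enrolling 90 would mean testing about 90/0.608 = 148 patients at the large-bias end of the assumed range and 90/0.991 = 91 at the slight end. The entry rule itself already requires that testing. The decision is needed before recruitment, which section 2.13 says had not begun, because screening results that are discarded cannot be recovered.
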